### Concealment mechanism {16b}

The block size will not be disclosed to study staff who are enrolling patients.

### Implementation {16c}

The allocation sequence is determined a priori by a biostatistician. The MT will be responsible for the randomization process and patient allocation.

## Assignment of interventions: blinding

### Who will be blinded {17a}

Blinding of patients and MTs to the intervention is not possible. However, outcomes at hospital discharge and after discharge will be collected by assessors blinded to allocation.

### Procedure for unblinding if needed {17b}

N/A. There is no indication of unblinding the blinded assessors. 

## Data collection and management

### Plans for assessment and collection of outcomes {18a}

#### Primary outcome: Short Physical Performance Battery

The initial SPPB will be administered by the MT enrolling the patient as part of the baseline assessment. The final SPPB will be administered by a physical therapist or exercise physiologist blinded to the patient’s treatment group allocation. All assessors will be trained by the primary study physical therapist ([name]). Acceptable inter-rater reliability of the SPPB has been shown in prior studies, [59, 60] but we will assess inter-rater reliability for the first 10 patients enrolled with each mobility tech as a quality check; the primary study physical therapist ([name]) will be the second assessor.

#### Secondary hospital clinical outcomes

Patients’ hospital discharge disposition, length of stay, and the presence of hospital-acquired complications (falls, venous thromboembolism, pressure ulcers, and hospital-acquired pneumonia) will be assessed retrospectively using medical record data, using a unique encounter number to identify study episodes. This number will also be matched to episode-level billing data to identify the cost of the hospital stay.

To characterize the mobility of both randomized groups, each patient will wear a medical grade accelerometer to directly record all movement throughout their hospital stay. The MT will place the accelerometer on the patient’s wrist like a watch (for better compliance and more accurate sleep measurement) with a sampling frequency of 90 Hz and an LFE filter. The device is highly water resistant and does not need to be removed for bathing. It will not display any information to the patient and the patient need not take any action. Raw acceleration data will be translated via algorithms into meaningful activities, including steps taken, energy expenditure, activity bouts, sedentary bouts, body position, sleep latency, total sleep time, wake after sleep onset, and sleep efficiency. Data will be downloaded from each device by the MT at least weekly and at discharge. Except for the random subset of 10–20% of patients who will continue to wear the device at home for an additional 10 days after discharging home, devices will be collected at discharge.

#### Secondary post-hospital outcomes

At 30 days post-discharge, a research assistant will contact participants to collect the additional secondary outcomes (FRAIL, Katz ADL, Lawton IADL, AM-PAC mobility, PROMIS physical function, and 30-day readmission). Contact will be initiated by subjects’ preferred means of communication, including telephone, email, patient portal, or text. Participants will be compensated for their time to respond. Based on preliminary efforts, we anticipate being able to contact 90% of the patients in 30 days. If we are unable to contact the patient, we will mail them the survey to complete on paper and return to our study team.

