### Sample size {14}

A sample size of 3000 has >99% power to detect a difference in SPPB change as small as 0.54 points (the MCID) between the two groups at a two-sided alpha of 0.05, assuming a common SD of 2.7 for the SPPB change, 20% non-compliance, 10% dropouts, and an interim analysis. The estimates for MCID and SD are based on observation of older acute care medical patients [43, 44]. Using these same assumptions, the power is still 92% for detecting a smaller difference of 0.35. Therefore, we expect ample statistical power for analyzing the primary outcome. The main reason for selecting this sample size is to ensure that the analyses of important secondary outcomes are not underpowered. The most important of these is discharge disposition, because even a small absolute difference in the number of patients discharged to home, as opposed to a skilled nursing facility, is clinically important. We will be able to detect a 7% difference in discharge to home vs. SNF with 98% power.

For other binary secondary outcomes (a combination of venous thromboembolism, pneumonia and falls, 30-day mortality, or 30-day readmission), the study will have 85% power to detect a 33% reduction assuming an 8% rate in the control group. Because these outcomes are not contingent on patient cooperation, we anticipate no dropouts. For secondary continuous outcomes such as length of stay, assuming 20% non-compliance rate, the power to detect a 4-h difference (0.167 days) is 95%.

Regarding the cost analysis, there is no accepted way of doing a power calculation. However, we tried adding $300 (an approximation of the cost of the intervention) to the costs of each of 1500 patients drawn randomly from a sample of 3000 Cleveland Clinic medical inpatients over the age of 65 with an AM-PAC 6-Clicks score between 16 and 20. We then performed a *t*-test on the log-transformed costs, as described in the economic analysis section, and we were able to detect the increase with a p-value of 0.03, indicating that should the intervention increase costs by an amount equal to the cost of the intervention, we should be able to identify it. Similarly, if the intervention decreases total costs by $300 or more (not including the costs of the intervention), we should have sufficient power to detect it.

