## Assignment of interventions: allocation

### Sequence generation {16a}

Randomization will be done using a computerized system. A block randomization scheme with a size of 4 will be used to ensure approximately equal numbers of patients per group. Allocation will be stratified within units within hospitals.

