#### Retention after discharge

Participation in the trial includes consenting to being contacted at 30 days in order to complete surveys regarding mobility, ADLs, and frailty. Subjects will be asked at enrollment for their preferred means of contact, including telephone, email, patient portal, or text message. Patients who are discharged alive will be reminded at discharge that they will be contacted at 30 days and that they will be compensated $20 for their time. Members of the study team will make 3 attempts to contact each patient using all methods that the patient has supplied. In preparation for this study, we attempted to contact 20 patients who met our proposed inclusion criteria and were able to successfully engage 18/20 patients at 30 days. If we are not able to reach a patient by these means, we will examine the EHR and “Care Everywhere,” which includes records for all hospitals using EPIC, to see whether the patient is currently hospitalized. If all of these methods fail, we will send a registered letter. Once contact is made, the team member will remind the patient of the commitment that they made at enrollment to provide these data and of the importance of their data to the success of the study. They will thank them for their time and their contribution to the scientific endeavor. If a relative indicates that the patient is deceased or has been transferred to long-term care, we will note that. If possible, we will contact them in the long-term care facility. Patients who cannot be reached by any means or refuse to provide their data will be considered lost to follow-up. For patients who cannot be reached, we will attempt to identify their vital status and whether they are in a long-term care facility based on their Medicare claims data or the EHR.

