### Methods for additional analyses (e.g., subgroup analyses) {20b}

We will conduct three sensitivity analyses to account for (1) missing outcomes data, (2) treatment heterogeneity by site, and (3) the dose-response curve in the intervention group.

To identify the patients most likely to benefit from ambulating with a MT, we will build models separately for each treatment arm to predict the outcome of at least 1-point increase in the SPPB (i.e., beyond the minimal clinically important difference). Using the predicted probabilities resulting from these models, we will develop a Classification and Regression Tree (CART) that should identify subsets of patients likely to benefit, not benefit, or be harmed by the treatment. For example, the analysis might show that female patients aged >75 years who have an initial 6-Clicks score between 16 and 18 have an estimated treatment benefit of being 22% more likely to achieve the 1-point increase in SPPB. Essentially the tree will form risk groups of patients with shared characteristics that should receive a similar care recommendation.

We will estimate the total cost of the episode of care including the index admission (from hospital cost accounting systems) and all non-medication costs for the 30 days following enrollment (from Medicare claims) for all patients. For the intervention group, we will add the personnel costs for the MTs (hourly wages plus benefits). Since cost data are skewed, our cost estimates will be transformed and then compared between groups using the *t*-test.

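### Thirty-day readmission is collected by contacting the patient, yet it is powered as an outcome that needs no patient cooperation and has no dropouts

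*Protocol article*

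**What the plan says.** Protocol article, Secondary post-hospital outcomes: a research assistant contacts participants to obtain "FRAIL, Katz ADL, Lawton IADL, AM-PAC mobility, PROMIS physical function, and 30-day readmission". The expected yield is stated: "we anticipate being able to contact 90% of the patients in 30 days". A paper survey is mailed to those not contacted.

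Protocol article, Retention after discharge: three contact attempts are made, then the EHR and Care Everywhere are checked for a current hospital stay, then a registered letter is sent. After that, "Patients who cannot be reached by any means or refuse to provide their data will be considered lost to follow-up". For unreached patients, claims or the EHR are used for vital status and long-term care residence. Readmission is not named there.

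Protocol article, Sample size {14}: 30-day readmission is one of the binary secondary outcomes given 85% power for a 33% reduction from an 8% control rate. The justification for assuming no loss is: "Because these outcomes are not contingent on patient cooperation, we anticipate no dropouts".

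Protocol article, Methods for additional analyses {20b}: the cost analysis takes "all non-medication costs for the 30 days following enrollment (from Medicare claims) for all patients". Medicare coverage, traditional or Advantage, is an inclusion criterion for that purpose (Eligibility criteria {10}).

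Outcomes {12} says only that readmission is assessed at the post-hospital time point and gives no source.

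**The concern.** An outcome obtained by contacting the patient depends on the patient answering. The mailed survey and the registered letter also need a response. The collection section therefore allows for missing readmission data that the power statement rules out.

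The article does name record-based collection where it intends it. Secondary hospital clinical outcomes takes disposition, length of stay and hospital-acquired complications from the medical record, and readmission is not in that list. The EHR check in the retention section does not fill the gap, because a patient readmitted and discharged again before the check is not currently in hospital.

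Two things are at stake: some power for a secondary outcome that the sample size was meant to support and, if missingness is related to readmission, the accuracy of the rate and of the comparison between arms. The trial already plans access to sources that would avoid most of this.

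**Working it through.** **Inputs.**
- Total sample size 3000 (Sample size {14}: "A sample size of 3000 has >99% power to detect a difference in SPPB change as small as 0.54 points").
- Blocks of 4 are used "to ensure approximately equal numbers of patients per group" (Sequence generation {16a}), so 1500 per arm.
- Alpha is set for the primary outcome "at a two-sided alpha of 0.05". I assume it carries over to the binary secondary outcomes.
- Control rate 8%, reduction 33%, no dropouts, stated power 85% (Sample size {14}).
- Contact rate 90% (Secondary post-hospital outcomes), based on 18 of 20 patients (Retention after discharge).

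**Step 1. Reproduce the stated power.** Pooled two-proportion test, with no dilution for non-compliance:

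power = Φ{ [ |p1 − p2| − 1.96·√(2p̄(1 − p̄)/n) ] / √[(p1(1 − p1) + p2(1 − p2))/n] }

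Reading 33% as one third: p1 = 0.08, p2 = 0.0533, p̄ = 0.0667, n = 1500.
- Difference: 0.02667
- Null term: 1.96 × √(0.12444/1500) = 1.96 × 0.009108 = 0.01785
- Alternative standard error: √(0.12409/1500) = 0.009095
- (0.02667 − 0.01785)/0.009095 = 0.969, so power = 83.4%

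Reading 33% as exactly 0.33 (p2 = 0.0536) gives 82.6%. The stated 85% is thus approximately matched, and only with zero loss.

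**Step 2. Apply the 10% non-contact.** n = 0.90 × 1500 = 1350 per arm.
- Null term: 1.96 × √(0.12444/1350) = 0.01882
- Alternative standard error: √(0.12409/1350) = 0.009587
- (0.02667 − 0.01882)/0.009587 = 0.819, so power = 79.4% (78.5% with p2 = 0.0536)

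If mail recovers half of those missed (an assumption), n = 1425 per arm and power is 80.6% to 81.5%.

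| Analysed per arm | Power |
|---|---|
| 1500 (no loss) | 82.6% to 83.4% |
| 1425 (5% loss) | 80.6% to 81.5% |
| 1350 (10% loss) | 78.5% to 79.4% |

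**Step 3. Number without a status.** 0.10 × 3000 = 300 before the mailed survey and registered letter. The exact 95% confidence interval for 18/20 is 68% to 99%, so the contact rate itself is uncertain in both directions.

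**Step 4. Illustrate selective loss.** Let q be the probability of reaching a readmitted patient, with overall contact held at 90%. The observed rate is 0.08·q/0.90.
- q = 0.90: 8.0%
- q = 0.80: 7.1%
- q = 0.70: 6.2%

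With equal true rates, q = 0.80 in one arm and 0.70 in the other would give 7.1% against 6.2%, a gap of 0.9 points. The design difference is 2.6 to 2.7 points. The values of q are assumptions; the protocol gives none.

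**Step 5. Check the window.** Participant timeline {13} places follow-up 30 days after enrollment, and the claims extract covers the same 30 days. Secondary post-hospital outcomes places the contact 30 days after discharge. If readmission is counted from discharge, a patient discharged on day 10 has only 30 − 10 = 20 post-discharge days in the planned extract.

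**The case against.** The contact-based reading may be an accident of drafting. Recruitment {15} and Retention after discharge describe the 30-day contact as covering mobility, daily activities and frailty, without readmission. The list in the collection section could be a loose inventory of 30-day outcomes, with the source of readmission left to a fuller protocol. The sample size statement fits a records source, and the claims already planned would contain readmissions. This stands as a possible explanation of intent, but the one place that gives a source for readmission says contact, so the text still needs correcting.

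The retention section also takes steps for the groups most likely to be missed: the check for a current hospital stay, contact inside long-term care, and noting deaths reported by relatives. Post-discharge outcomes are to be collected by blinded assessors (Who will be blinded {17a}). These steps limit the problem, though none of them records a completed readmission in an unreached patient.

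A reader might infer that 300 patients will have no readmission status, or that readmission will be undercounted or biased. The documents support neither. The 300 comes before the mailed survey and letter, and nothing in the protocol says that readmitted patients are harder to reach or that reach differs by arm. A reader might also infer that using claims would make the no-dropout statement true. The Discussion expects some missing data in the cost analyses, so that does not follow.

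**Conclusion.** The inconsistency holds on the text: the same outcome is collected by patient contact in one section and powered as independent of patient cooperation in another. The effect on power is modest, about 79% with 10% loss against about 83% with none (85% stated), and smaller if mail recovers some patients. These figures assume two-sided 0.05, 1500 per arm and no dilution for non-compliance. Selective loss is possible and could matter as much as the lost power, but its size rests wholly on assumed reach rates: 6.2% to 7.1% observed for a true 8% if 70% to 80% of readmitted patients are reached. The primary outcome is not affected. The change should be made because this outcome carries its own power claim and most of the data for a better source are already being obtained.

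**What to change.** 1. In Outcomes {12} and Secondary post-hospital outcomes, make Medicare claims plus the EHR and Care Everywhere the primary source of 30-day readmission for all randomised patients, extracted in the same way and blind to arm. Take readmission off the contact-dependent list.
2. Use patient-reported admissions only when confirmed against records, or in a sensitivity analysis. Adding them unconfirmed to the main endpoint would bring back the dependence on contact.
3. State one readmission window. Reconcile the 30 days from enrollment in Participant timeline {13} and the claims extract with the 30 days from discharge in Secondary post-hospital outcomes. If the window runs from discharge, extend the claims extract.
4. In Sample size {14}, replace the no-dropout statement for readmission with the expected completeness of the records. If collection by contact is kept, restate the power at about 79%.

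The cost is protocol wording and one more variable from extracts already planned, plus a longer extract if the window runs from discharge. The downside is small: claims arrive late and will be incomplete for some patients, which EHR data can partly offset.

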### Plans to promote participant retention and complete follow-up {18b}

#### Retention in the hospital

Each day, MTs will visit patients in the intervention arm until they have ambulated 3 times or the MT has made 4 attempts. They will consult with daily schedules to avoid visiting while patients are sleeping, eating, or having procedures. Daily step counts and other activities will be collected automatically from the accelerometer worn by the patient on the wrist. It is waterproof and can be worn continuously, so patients are not required to take any action to participate. In our pilot, we had very few patients withdraw during hospitalization. We do not anticipate this will be a problem. If it is, we will assess patient reasons for discontinuing and craft strategies to address those issues.

#### Retention after discharge

Participation in the trial includes consenting to being contacted at 30 days in order to complete surveys regarding mobility, ADLs, and frailty. Subjects will be asked at enrollment for their preferred means of contact, including telephone, email, patient portal, or text message. Patients who are discharged alive will be reminded at discharge that they will be contacted at 30 days and that they will be compensated $20 for their time. Members of the study team will make 3 attempts to contact each patient using all methods that the patient has supplied. In preparation for this study, we attempted to contact 20 patients who met our proposed inclusion criteria and were able to successfully engage 18/20 patients at 30 days. If we are not able to reach a patient by these means, we will examine the EHR and “Care Everywhere,” which includes records for all hospitals using EPIC, to see whether the patient is currently hospitalized. If all of these methods fail, we will send a registered letter. Once contact is made, the team member will remind the patient of the commitment that they made at enrollment to provide these data and of the importance of their data to the success of the study. They will thank them for their time and their contribution to the scientific endeavor. If a relative indicates that the patient is deceased or has been transferred to long-term care, we will note that. If possible, we will contact them in the long-term care facility. Patients who cannot be reached by any means or refuse to provide their data will be considered lost to follow-up. For patients who cannot be reached, we will attempt to identify their vital status and whether they are in a long-term care facility based on their Medicare claims data or the EHR.

### Data management {19}

Study data at all sites will be collected and managed using REDCap electronic data capture tools hosted at Cleveland Clinic [61, 62]. REDCap (Research Electronic Data Capture) is a secure, web-based software platform designed to support data capture for research studies, providing (1) an intuitive interface for validated data capture, (2) audit trails for tracking data manipulation and export procedures, (3) automated export procedures for seamless data downloads to common statistical packages, and (4) procedures for data integration and interoperability with external sources.

### Confidentiality {27}

Patient confidentiality will be maintained throughout the clinical study in a way that ensures the information can always be tracked back to the source data. For this purpose, a unique subject identification code (ID number and subject name code) will be used that allows the identification of all data (such as survey responses and scales) reported for each subject. Subject information collected in each phase of the proposed work will comply with the standards for the protection of privacy of individually identifiable health information as promulgated in the Health Insurance Portability and Accountability Act and as mandated in Title 45 CFR, Parts 160 and 164. All records will be kept confidential and no physician or patient name will be released by study staff at any time.

Returned paper surveys or telephone responses will be entered into REDCap for secure electronic storage, and paper copies of surveys will be locked in a cabinet in the offices of the Center for Value-Based Care Research. REDCap is protected behind a login and Secure Sockets Layer (SSL) encryption. Data collection is customized for each study or clinical trial based on a study-specific data dictionary defined by the research team. REDCap requires a password for entry. Patient-level data access will be available only to those members of the team directly involved in data collection or analysis. All electronic data systems are maintained behind the Cleveland Clinic firewall. Entry to the continually locked research area is restricted by a coded badge identification system.

### Plans for collection, laboratory evaluation, and storage of biological specimens for genetic or molecular analysis in this trial/future use {33}

N/A. We are not collecting biospecimens.

## Statistical methods

### Statistical methods for primary and secondary outcomes {20a}

#### Statistical analyses

The main analysis will follow the intention-to-treat principle. The primary outcome, change in the SPPB from baseline to discharge (or 10 days), will be compared between the groups using an independent samples *t*-test. The large sample size should ensure that any confounding variables are equally distributed between groups. However, if we identify that any baseline variables are unbalanced and also associated with the outcome, we will model SPPB using a linear mixed-effects model to control for potential confounding. The fixed effects will include group, measurement time point, their interaction, site, and any unbalanced baseline variables. Secondary binary outcomes (discharge disposition and hospital-acquired complications) will be assessed using the chi-square test. The secondary longitudinal outcome (mobility improvement 30 days after hospital discharge) will be modeled using linear mixed-effects models.

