**Methods:**

The AMBULATE study is a multicenter, single-blind, parallel control design, individual-level randomized trial. It will include patients admitted to a medical service in five hospitals in two regions of the USA. Patients over age 65 with mild functional deficits will be randomized using a block randomization scheme. Those in the intervention group will ambulate with the MT up to three times daily, guided by the Johns Hopkins Mobility Goal Calculator. The intervention will conclude at hospital discharge, or after 10 days if the hospitalization is prolonged. The primary outcome is the Short Physical Performance Battery score at discharge. Secondary outcomes are discharge disposition, length of stay, hospital-acquired complications (falls, venous thromboembolism, pressure ulcers, and hospital-acquired pneumonia), and post-hospital functional status.

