### Methods in analysis to handle protocol non-adherence and any statistical methods to handle missing data {20c}

Outcomes will be assumed missing at random in the main analysis. We will perform one sensitivity analysis in which we impute missing outcomes using a chained equation approach, and another using the marginal structure model (MSM), which can handle possible bias introduced by noncompliance in the intervention group and informative censoring/dropout simultaneously.

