Many potential limitations for our study are mitigated by the study’s design. For example, patients who are enrolled may be unable or unwilling to ambulate three times each day. If adherence is lower than expected in interim analyses, we will compare adherence rates across sites and attempt to identify and spread best practices. If that is not successful, we would still likely have sufficient power to detect a difference in our primary (>99% power with 70% adherence) and secondary outcomes (80% power with 70% adherence). Depending on the ease of enrollment, we may decide to enroll additional patients with the same resources. We anticipate heterogeneous patients, sites, and controls. Given our large sample, we anticipate that all of these important covariates will be balanced between the intervention and control arms. If we find that they are not, we will adjust our outcomes for important confounders. If we are unable to directly identify subgroups for whom the intervention is most beneficial, we will create a score, based on logistic regression, to identify patients who benefit if they score above a certain threshold. Alternatively, we will provide recommendations and tools to enable individual hospitals to incorporate our prediction model into the electronic health record and identify patients directly from the model.

While functional decline in the hospital is multifactorial, general out-of-bed mobility is a modifiable factor for many patients. This randomized controlled trial will test the effectiveness of MT-assisted ambulation on outcomes that matter to both patients and hospitals, including functional status, hospital discharge disposition, and the incidence of potentially avoidable hospital complications. It will also provide a useful estimation of cost implications to help hospital administrators assess the feasibility and utility of creating MT positions in their own hospitals.

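### The primary SPPB comparison would be more precise, and fixed before outcomes are seen, as one baseline-adjusted ANCOVA; the imbalance-triggered mixed model as written does not adjust the change contrast

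*Protocol article*

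**What the plan says.** The Statistical analyses section (item 20a) sets the primary test: "The primary outcome, change in the SPPB from baseline to discharge (or 10 days), will be compared between the groups using an independent samples" t-test. It then adds a contingency: "if we identify that any baseline variables are unbalanced and also associated with the outcome, we will model SPPB using a linear mixed-effects model". That model is specified as follows: "The fixed effects will include group, measurement time point, their interaction, site, and any unbalanced baseline variables". The Discussion repeats the contingency for imbalanced covariates: "If we find that they are not, we will adjust our outcomes for important confounders".

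Under Sequence generation (item 16a), allocation is in blocks of four, and "Allocation will be stratified within units within hospitals". The t-test uses neither hospital nor unit. The fallback model names site but not unit. Discharge disposition and complications are compared by chi-square tests, also without strata.

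Item 20a and the Outcomes section (item 12) define the primary outcome as change in SPPB. The abstract says: "The primary outcome is the Short Physical Performance Battery score at discharge".

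**The concern.** Three features of the stated plan could be better at no cost.

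- **Precision.** A change score fixes the coefficient of baseline SPPB at 1. ANCOVA estimates it, and in large samples is never less precise. Hospital and unit, which define the randomisation strata, are also unused in the primary test.
- **A model chosen from outcome data.** Whether a baseline variable is related to the outcome can be judged only after outcomes are seen, so the rule cannot be applied in advance. It could also fire at one look and not the other, in which case the interim and final statistics would come from different models.
- **A fallback that misses its purpose.** It is meant to control confounding, but its covariates enter only as main effects, beside the group-by-time interaction that carries the treatment effect on change.

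At stake are the width of the primary confidence interval and an unambiguous primary result. The validity of the t-test is not in question.

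**Working it through.** **Inputs.** From Sample size (item 14): 3000 patients, SD of change 2.7, 10% dropout, two-sided alpha 0.05, differences of 0.54 and 0.35 points. From Interim analyses (item 21b): one look at 40% with boundary 3.35. Assumed, because the protocol does not give it: the correlation r between baseline and final SPPB, taken as 0.5 and 0.8, with equal variances at the two times.

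**1. The plan's own power.** With 1500 × 0.9 = 1350 per arm, SE = 2.7 × √(2/1350) = 0.1039.
- For 0.35: 0.35/0.1039 − 1.96 = 1.41, power 0.920. The stated 92% reproduces.
- For 0.54: power 0.9994. The stated >99% reproduces.
- Allowing for the interim boundary, the final critical value is 1.962, and power for 0.35 stays at 0.920.

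**2. Variance ratio.** With common SD s, Var(change) = 2s²(1 − r) and the ANCOVA residual variance is s²(1 − r²). The ratio is (1 + r)/2. If the SDs differ (s₀ at baseline, s₁ at the end), the change-score variance exceeds the ANCOVA variance by (s₀ − r·s₁)², which is never negative.

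**3. Effect on this trial (1350 per arm).** The ANCOVA residual SD is 2.7 × √((1 + r)/2).

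| Analysis | Variance ratio | SD | Power for 0.35 | 95% CI half-width | n per arm for the t-test's precision |
|---|---|---|---|---|---|
| t-test on change | 1 | 2.700 | 0.920 | 0.204 | 1350 |
| ANCOVA, r = 0.5 | 0.75 | 2.338 | 0.973 | 0.176 | 1013 |
| ANCOVA, r = 0.8 | 0.90 | 2.561 | 0.944 | 0.193 | 1215 |

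Any gain from hospital and unit would be additional. It cannot be sized, because the documents give no between-unit variation.

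**4. The fallback model.** For patient i at time t (0 or 1), the listed fixed effects are a + b·groupᵢ + c·t + d·groupᵢ·t + θ·xᵢ, where x stands for site or an unbalanced covariate. Subtracting time 0 from time 1 leaves c + d·groupᵢ. The x term cancels, so with complete data d is estimated by the raw difference in mean change. In a simulated data set with 300 per arm, a covariate shifted between arms and a random intercept per patient, the group-by-time estimate was 0.4696 with the covariate and 0.4696 without it, equal to the raw difference. On the same data, ANCOVA moved from 0.586 to 0.329 when the covariate was added, so the covariate did matter.

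**5. Type I error of the two-step rule.** Null simulation: 4000 runs at each r of 0.3, 0.6 and 0.8; 1350 per arm; baseline SPPB plus ten weak prognostic covariates; 5% thresholds for both imbalance and association. The thresholds and covariates are assumptions, and the triggered covariates were added to a regression on change. The trigger fired in 42% to 44% of trials. Rejection rates, with simulation error of about 0.0035:
- t-test: 0.052 to 0.056
- ANCOVA: 0.051 to 0.059
- two-step rule: 0.042 to 0.048
- better of the t-test and two-step p-values: 0.055 to 0.062

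**The case against.** The strongest reply is that nothing in the primary test is wrong. Under randomisation the t-test on change is unbiased, and ignoring strata errs, if anything, towards caution. Power at the stated MCID is above 99%, and item 14 says the sample size was driven by secondary outcomes. The imbalance threshold and covariate list are details that an unseen SAP may hold. All of this stands, so the point is an efficiency gain and a fixed analysis, not the correction of an invalid one. What the reply does not cover is the trigger itself, which the protocol states and which needs outcome data, and the fallback's listed terms.

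Some stronger readings are tempting but not supported:

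- **Inflated type I error.** The two-step rule did not inflate it in the simulation. Even picking the better p-value gave at most 0.062.
- **A power shortfall that ANCOVA rescues.** If the 20% non-compliance also diluted 0.35 to 0.8 × 0.35 = 0.28, the t-test would have power 0.769, and ANCOVA 0.875 (r = 0.5) or 0.811 (r = 0.8). That is a separate question about item 14. The stated 92% reproduces with 0.35 as the between-arm difference and is the right comparator here.
- **Missing outcomes left unhandled.** Item 20c says "Outcomes will be assumed missing at random in the main analysis". A t-test on available changes conditions only on arm, but the same section plans chained-equation imputation and a marginal structural model as sensitivity analyses.
- **An unsettled primary outcome.** Items 12, 14 and 20a all use change; only the condensed abstract says score. This is a minor wording difference.
- **A known loss from ignoring strata.** Its direction is clear where strata predict outcome; its size is not.

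**Conclusion.** The point holds as a free improvement. The primary t-test is valid but less precise than it need be, its replacement is triggered by outcome data, and the replacement as listed leaves the complete-data change contrast unadjusted.

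ANCOVA would lower the variance by 25% at r = 0.5 and by 10% at r = 0.8, narrowing the confidence interval half-width by 0.028 or 0.011 points (from 0.204). These figures rest on an assumed r, equal variances and 1350 analysed per arm. The cancellation in the fallback rests on complete data and on reading the listed covariates as main effects, which is how they are written.

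**What to change.** - Name one primary analysis, used at both the interim and final looks: ANCOVA of SPPB at discharge or day 10 on arm, baseline SPPB and hospital, with unit as a random effect and small units pooled within hospital by a stated rule. Score and change then give the same treatment effect, which settles the abstract's wording.
- Drop the imbalance-triggered step, or label it a sensitivity analysis. If kept, it must let covariates act on the change contrast, through covariate-by-time terms or by entering them in the ANCOVA.
- Use Mantel-Haenszel tests stratified by hospital for discharge disposition and complications.
- Keep the imputation and marginal structural model analyses already planned under item 20c.

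The cost is wording in the protocol and SAP, plus the pooling rule for sparse units. Baseline SPPB, hospital and unit are already recorded, and neither the sample size nor data collection changes.
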